### 9.3 Study Interim Analysis

The current study will have a single interim analysis which will take place at the completion of the recruitment and follow-up of 60% of the total number of subjects (i.e. 312). The interim analysis is designed to test for early stopping for futility or efficacy as well as for sample size re-estimation. The interim analysis and final analysis will be based on the method of the sum of the stage wise p-value discussed in Mark and Chang, 2008. The table below, describe the interim analysis testing boundaries.

| Boundary      | Decision                                                                                                       |
|---------------|----------------------------------------------------------------------------------------------------------------|
| Alpha1 = 0.01 | Stop the trial for early efficacy if the interim analysis p-value is less than 0.01                            |
| Beta1 =0.25   | Stop the trial for futility if the interim analysis P-value is equal to or larger than 0.25                    |
| Alpha2=0.1832 | Declare the trial significant if the sum of the interim analysis and final stage P-values are less than 0.1832 |

The sample size Re-estimation will be based on the ratio of the planned effect size to the observed effect size from the interim analysis according to the following formula:

$$N = \left( \frac{E_0}{E} \right)^a N_0$$

Where a is a constant which will be set to 2 and  $N_0$  is a number chosen to be slightly larger than the classical sample size per group,  $E_0$  is the planned effect size of .7 and E is the observed effect size from the interim analysis.

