### 9.2 Sample Size and Power Considerations

#### 9.2.1 Assumptions and Study Hypothesis:

- a. **Time to discharge or clinical improvement by 2 points** in the standard of care arm is expected to be (median: 11 days; Cai Q, Y.M., Liu D, Chen J, Shu D, Xia J, , Experimental Treatment with Favipiravir for COVID-19: An Open-Label Control Study. 2020.).
- b. The exact treatment effect from Favipiravir tables + Hydroxchloroquine is not exactly known but can be approximated using prior clinical studies. A study comparing the effect of Favipiravir to lopinavir/ritonavir on virus clearance has shown a 64% reduction in time to viral clearance in the Favipiravir arm. This was equivalent to a median of 11 days. We assume that clinical improvement might take place a little later to viral clearance and therefore we assume that the treatment arm might result in a minimum clinically meaningful expected reduction of 30% (Median 7.7 days). This is equivalent to a Hazard ratio of 0.7.

- c. We further assume, that 50% of the patients in the control group will have clinical improvement/ discharged and 70% will have clinical improvement/discharged in the treatment arm
- d. It is anticipated that very few of these subjects will be randomized and not start study treatment (and so be excluded from the primary analysis) or be lost to follow-up (and so have missing data for the primary endpoint). Given certain uncertainties however, we have included a nominal 10% drop out rate.
- e. The primary hypothesis of the current study is  $H_0: HR = 1$  vs.  $H_1: HR \neq 1$  ; and HR is the hazard ratio of treatment compared to control arm.

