#### 9.2.2 **Sample Size Estimation for Classical Two Arm Parallel Design:**

Under the classical two arms parallel design the total effective sample sizes needed is 472 subjects (236 subjects per group). The Estimated sample size achieve 85 % power to detect a minimum of 30% reduction in the median time, to clinical improvement by at least two points or hospital discharge, in the treatment group compared to the control group. The median time in the treatment arm is 11 days under the null hypothesis and 7.7 days under the alternative hypothesis. The median time in control group under the null hypothesis is 11 days. The two survival curves will be analyzed using one sided cox proportional hazard regression. The significance level of the test is 0.025. Assuming 10% drop out rate, the overall sample size for the trial is estimated to be 520 (260 per group). Sample size adjustment will be considered after interim analysis of 60% of the subjects' recruitment and based on DSMB recommendation.

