### Analysis of the primary endpoint:

The primary endpoint of the current study is Median time to clinical improvement by at least 2 points or discharge from the hospital. The number and percent of subjects who met the endpoint by day 28 of follow up will be calculated and tabulated. Kaplan-Meier plot of time from randomization to endpoint will be generated (censoring at 28 days if completed follow-up, or at date of last contact if lost to follow-up prior to 28 days), with associated table showing: number censored and number (%) meeting the endpoint, median time to endpoint and associated HR with 95% confidence interval; p-value from cox proportional hazard regression.

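### The interim futility bound (0.25) lies above the final success bound (0.1832), so an interim p-value from 0.1832 up to 0.25 continues a trial that can no longer succeed; separately, the only stated power is for the single-look design

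*Protocol*

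**What the plan says.** Protocol section 9.3 plans one interim analysis, after 60% of subjects (312 of 520) have been recruited and followed up. It serves early efficacy, futility and sample size re-estimation, and both the interim and the final test rest on the sum of stage-wise p-values. The boundary table stops for efficacy at an interim p-value below 0.01. For futility it says "Stop the trial for futility if the interim analysis P-value is equal to or larger than 0.25". For the final analysis it says "Declare the trial significant if the sum of the interim analysis and final stage P-values are less than 0.1832".

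Section 9.2.2 gives the sample size: "Under the classical two arms parallel design the total effective sample sizes needed is 472 subjects (236 subjects per group". It continues: "The Estimated sample size achieve 85 % power to detect a minimum of 30% reduction in the median time". The test is to be "analyzed using one sided cox proportional hazard regression", and "The significance level of the test is 0.025". The total becomes 520 after a 10% dropout allowance. Section 9.2.1 sets the effect: "This is equivalent to a Hazard ratio of 0.7". It assumes improvement or discharge in 50% of controls and 70% of treated patients, and item e states a two-sided alternative. No power is given for the two-stage rule of section 9.3.

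**The concern.** The two bounds do not fit together. Write p1 for the interim p-value and p2 for the second-stage p-value. Success after the interim requires p1 + p2 < 0.1832. Once p1 reaches 0.1832 the sum cannot fall below that limit, yet the table stops only at 0.25. Between the two values, patients would go on being randomised to an open-label experimental combination or control for a primary test whose outcome is already settled.

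A second, separate point is that the trial will be decided by the two-stage rule, while the only power in the protocol belongs to a single-look test. A reader planning from section 9.2 would take 85% as the power of the trial.

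**Working it through.** **Inputs.** Hazard ratio 0.7, event proportions 50% and 70% (mean 60%) from section 9.2.1; one-sided 0.025 and 472 effective subjects from section 9.2.2; 1:1 allocation; bounds 0.01, 0.25 and 0.1832 and the 60% interim from section 9.3. Only the size of the log hazard ratio enters the calculations.

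**1. The stated power, single look.** Events: 472 × 0.60 = 283.2. Drift: √(283.2/4) × ln(1/0.7) = 8.414 × 0.3567 = 3.001. Power: Φ(3.001 − 1.960) = 85.1%. The 85% reproduces for the classical design.

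**2. Type I error of the table.** For independent stage-wise p-values and any futility bound of 0.1832 or more:

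α = 0.01 + (0.1832 − 0.01)²/2 = 0.01 + 0.0150 = 0.0250.

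The 0.1832 is therefore correctly derived. The result is the same for futility bounds of 0.1832 and 0.25, because no p1 between them can lead to success.

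**3. The gap.** If 0.1832 ≤ p1 < 0.25, then p1 + p2 ≥ 0.1832 for every possible p2. This needs no assumption.

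**4. Chance of landing in the gap.** With interim drift d1 = √(283.2/4) × |ln HR| × √0.6, and normal quantiles 0.903 (for 0.1832) and 0.674 (for 0.25), the probability is Φ(0.903 − d1) − Φ(0.674 − d1). The 283.2 events and the 60% information fraction are held fixed.

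| True hazard ratio | d1 | Probability |
|---|---|---|
| 1.00 | 0 | 0.25 − 0.1832 = 6.7% |
| 0.90 | 0.687 | 9.1% |
| 0.85 | 1.059 | 8.8% |
| 0.80 | 1.454 | 7.3% |
| 0.70 | 2.325 | 0.0776 − 0.0495 = 2.8% |

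Under no effect, the gap holds 0.0668/0.24 = 28% of all trials that continue past the interim. Patients still to be enrolled on the planned total: 520 − 312 = 208.

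**5. Power of the two-stage rule at hazard ratio 0.7, 472 evaluable, no re-estimation.** Stage drifts: 3.001 × √0.6 = 2.325 and 3.001 × √0.4 = 1.898.

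- Success at the interim: Φ(2.325 − 2.326) = 49.9%.
- Success at the end: integrating P(p2 < 0.1832 − p1) over p1 from 0.01 to 0.1832 gives 32.0%.
- Total: 81.9%. A simulation of 4 million trials gives 82.0%.

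With the futility bound at 0.1832 the total is again 81.9%. Other bases:

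- 468 evaluable (520 × 0.9): 81.6%.
- All 520 evaluable: 85.4%.
- Interim information fraction from 50% to 70%, at 472: 80.0% to 82.7%.
- About 514 evaluable would be needed for 85%.

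**The case against.** The strongest reply is that the gap biases nothing. Type I error is 0.0250 as written, power is untouched, and at the planned effect the gap is reached in only 2.8% of trials. That stands, but it is also why the repair is free. It does not justify continuing enrolment after the result is fixed.

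Nor are 208 further patients certain. Re-estimation happens at the same look and may change the number. The protocol does not say that enrolment pauses while the first 312 are followed, so some of the 208 may already be randomised. The DSMB can also stop the trial. Hence the figure is an upper value on the planned total, subject to re-estimation.

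On power, a reader might infer that the 85% is a false claim, or that nobody ever worked out the two-stage power. The document supports neither. Section 9.2.2 labels the 85% as belonging to the classical design, and a separate analysis plan that is not shown may contain the other figure. Upward re-estimation could also recover power. The loss comes from the sum-of-p-values rule, not from the gap.

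A reader might also infer an inflated error rate because section 9.4 lists only a "p-value from cox proportional hazard regression", which could be taken as the second-stage p-value computed on all patients, or because item e of section 9.2.1 is two-sided. Section 9.3 says the p-values are stage-wise and section 9.2.2 says the test is one-sided, so the text does not adopt either reading. What remains is a wording mismatch.

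**Conclusion.** The boundary table is wrong as written. The contradiction is pure arithmetic, and since both numbers are fixed in section 9.3, a later analysis plan could not cure it without departing from the protocol. The probabilities, 6.7% under no effect and 2.8% to 9.1% for hazard ratios from 0.70 to 0.90, rest on 472 evaluable patients, a 60% event proportion, 60% of the information at the interim and one-sided p-values.

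The power point is smaller: about 82% rather than 85% at 472 evaluable before re-estimation. The shortfall disappears (85.4%) only if all 520 are evaluable, whereas the protocol sets the excess over 472 aside for dropout. This is a reporting gap of about 3 points, not an error in the classical calculation.

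**What to change.** - **Section 9.3:** set the futility bound to 0.1832. Type I error stays at 0.0250 and power does not change. A lower bound b is also possible if the final bound α2 is recalculated from 0.025 = 0.01 + α2(b − 0.01) − (b² − 0.01²)/2.
- **Section 9.2:** alongside the classical 85%, state the two-stage power of about 82% at 472 evaluable before re-estimation, with its assumptions.
- **Minor consistency edit:** align the two-sided alternative in item e of section 9.2.1 with the one-sided test in section 9.2.2. State in section 9.3 that p1 and p2 are one-sided and stage-wise, with p2 taken only from patients after the interim cohort.

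The cost is protocol wording, plus a stated power about 3 points lower. No patients are added.

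### The sample-size re-estimation rule in section 9.3 uses the hazard ratio itself, so it shrinks the trial as the interim effect weakens and costs about 7 to 8 points of power at the planned effect

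*Protocol*

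**What the plan says.** Section 9.3 plans one interim analysis at 312 subjects. It stops for efficacy if p1 < 0.01 and for futility if p1 ≥ 0.25. Otherwise the trial continues and succeeds at the end if p1 + p2 < 0.1832. The same section re-estimates the sample size by N = (E0/E)^a × N0. On the exponent it says: "Where a is a constant which will be set to 2". E0 "is the planned effect size of .7 and E is the observed effect size from the interim analysis". N0 "is a number chosen to be slightly larger than the classical sample size per group", with no figure given. No logarithm, minimum or maximum appears.

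Section 9.2.1 explains the 0.7. The median falls from 11 to 7.7 days, and "This is equivalent to a Hazard ratio of 0.7". It also states that "HR is the hazard ratio of treatment compared to control arm".

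Section 9.2.2 gives the classical size as 472 in total (236 per group), raised to 520 (260 per group) for 10% dropout. "The Estimated sample size achieve 85 % power", and "The significance level of the test is 0.025", one-sided. It adds that an adjustment will be considered after the interim on the DSMB's recommendation.

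**The concern.** The required number of events is inversely proportional to the square of the effect, so a ratio of squared effects can rescale a sample size. That holds only if the effect measure is zero under the null. The log hazard ratio is; the hazard ratio is not. With E0 = 0.7 and E an observed ratio, E rises towards 1 as the benefit fades and (0.7/E)^2 falls.

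Re-estimation exists to protect power when the interim effect is promising but smaller than planned. The printed rule does the opposite. Section 9.2 itself warns that a small departure from the assumed hazard ratio has a severe effect on power, so this is the situation in which the rule most needs to point the right way.

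**Working it through.** **Inputs.** From the protocol: ratio 0.7, one-sided 0.025, 85% power, 1:1 allocation, event proportions 50% and 70% (mean 60%), interim at 312, boundaries 0.01, 0.25 and 0.1832, a = 2. Assumed: N is the total per group; N0 is 236 to 260; interim p-values are one-sided; there is no floor on N, except that patients already enrolled (156 per group) stay in.

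**The plan's own figures reproduce.**
- Schoenfeld events: 4 × (1.960 + 1.036)^2 / (ln 0.7)^2 = 282.3, so 283. Then 283/0.60 = 471.7, giving 472, or 236 per group.
- 472 × 1.10 is about 520.
- Overall alpha: 0.01 + 0.5 × (0.1832 − 0.01)^2 = 0.0250.

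**Direction of the rule.** The correct multiplier on the log scale is (ln 0.7 / ln E)^2.

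| Observed ratio | As written, (0.7/E)^2 | Log scale |
|---|---|---|
| 0.60 | 1.36 | 0.49 |
| 0.70 | 1.00 | 1.00 |
| 0.75 | 0.87 | 1.54 |
| 0.80 | 0.77 | 2.55 |
| 0.85 | 0.68 | 4.82 |
| 0.90 | 0.60 | 11.5 |

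The log column agrees with the protocol's sizing method: at 0.80, Schoenfeld gives about 602 per group, and 602/236 = 2.55.

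**No other scale for E rescues E0 = 0.7.** At exactly the planned effect the formula should return N0.
- With E = |ln 0.7| = 0.357 it returns (0.7/0.357)^2 = 3.84 N0.
- With E = 1 − 0.7 = 0.3 it returns (0.7/0.3)^2 = 5.44 N0.
- With E = 11/7.7 = 1.43 it returns 0.24 N0.
- Only E as a ratio of 0.7 returns N0, and then the direction is reversed.

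**Where the rule acts.** Interim events are 312 × 0.6 = 187.2, and z1 = −ln(E) × √187.2/2 = −ln(E) × 6.841.
- p1 = 0.01 (z = 2.326): E = exp(−2.326/6.841) = 0.712, N/N0 = 0.97.
- p1 = 0.1832 (z = 0.903): E = 0.876, N/N0 = 0.64.
- p1 = 0.25 (z = 0.674): E = 0.906, N/N0 = 0.60.

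The trial therefore continues only for 0.712 to 0.906, always with N below N0. Above 0.876, p1 alone exceeds 0.1832 and the final test cannot succeed at any N. The range that matters is 0.97 to 0.64 of N0.

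**Power.** This was computed by numerical integration over z1, with independent stage-wise p-values and second-stage events 2 × (N − 156) × 0.6. At a true ratio of 0.7:

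| N0 per group | No re-estimation | As written | Loss (points) |
|---|---|---|---|
| 236 | 82.5% | 74.3% | 8.2 |
| 240 | 83.1% | 75.1% | 8.0 |
| 260 | 85.4% | 78.3% | 7.1 |

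With a 54% event rate the pairs are 79.0% and 71.7% (N0 = 240), and 81.6% and 74.9% (260). At a true ratio of 0.8 with N0 = 240 and 60% events they are 44.6% and 37.1%.

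**The case against.** **DSMB discretion.** Section 9.2.2 makes any adjustment a matter for the DSMB, which could decline a cut. That softens the consequence. It does not cure the rule, because the board would be handed a formula that recommends cutting an underperforming trial.

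**A later analysis plan could add limits.** It could, but the formula and the value 0.7 are fixed in the protocol. A floor at N0 alone would leave the re-estimation almost inert, since no continuing result raises N.

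**N may mean the second-stage size.** Section 9.3 does not say. On that reading, power at 0.7 would be about 91%, but the multiplier would still run the wrong way. Total per group is the more natural reading because N0 is tied to the classical size per group.

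**Stronger readings that the documents do not support.**
- A reader might infer that the second stage is usually almost empty. Among trials that continue at a true ratio of 0.7, N is at or below the 156 already enrolled in fewer than 10% (0.4% at N0 = 260, 7.6% at 240). Median N is about 193 to 213 per group.
- An observed ratio of 0.90 looks like a striking example because N falls below current enrolment when N0 is 236 or 240. But p1 is then about 0.236, so that trial is already lost whatever N is.
- A loss from 85% to 75% would compare 260 per group without re-estimation against N0 = 240 with it. Like for like, the loss is 7 to 8 points.
- Power near 54% with no second stage would require E0 = 0.7 and E above 1, opposite conventions in one ratio. The protocol consistently uses 0.7 for benefit, so that is a hazard of leaving the orientation unstated, not what the text prescribes.

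**Conclusion.** The formula is wrong as printed and must be corrected before the interim analysis. That its direction is reversed depends on none of the assumptions about N0, event rate or floor.

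The size does depend on them. With N as the total per group, 60% events, N0 of 236 to 260 and no floor, the rule as written leaves power of 74% to 78% at the planned effect. That is below the stated 85% and below the 80% that the sensitivity analysis in section 9.2 calls the accepted norm. More than half of trials at the planned effect (54.5%) stop early for efficacy and are untouched by the formula, which is why the loss is not larger. The harm is to power only; the boundaries still give one-sided 0.025.

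One related point needs settling in the same place. Improvement is a favourable event, so the treatment-versus-control ratio defined in section 9.2.1 would be 11/7.7 = 1.43 for the planned benefit, not 0.7.

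**What to change.** In section 9.3:
- Define E0 and E as log hazard ratios with one stated orientation, so that |E0| = ln(11/7.7) = 0.357. Align section 9.2.1 with it.
- State that N is the total per group and give N0 as a number.
- Do not allow N below the planned 260 per group.
- State a maximum N. The log-scale rule grows without limit as the ratio approaches 1 and already asks for about 4.8 × N0 at 0.85.

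If the sponsor wants no increase, delete the re-estimation and keep 260 per group. With the same interim boundaries, that gives about 85% power at 0.7 if all 260 are evaluable, and about 82.5% at 236 effective.

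The cost is a short amendment and a check of the operating characteristics for the chosen limits. Extra patients arise only if the maximum is set above 260 per group.

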## 9.4 Statistical Analysis

A detailed statistical analysis plan will be developed before undertaking any comparative analyses of outcomes. The following provides a brief summary of approach to analysis for the primary endpoint.

### Analysis of the primary endpoint:

The primary endpoint of the current study is Median time to clinical improvement by at least 2 points or discharge from the hospital. The number and percent of subjects who met the endpoint by day 28 of follow up will be calculated and tabulated. Kaplan-Meier plot of time from randomization to endpoint will be generated (censoring at 28 days if completed follow-up, or at date of last contact if lost to follow-up prior to 28 days), with associated table showing: number censored and number (%) meeting the endpoint, median time to endpoint and associated HR with 95% confidence interval; p-value from cox proportional hazard regression.

### For secondary endpoints:

- Quantitative variables such as duration of ICU stay and change from baseline in clinical scores, etc., are expected to have reasonably skewed distributions and may be subject to censoring (e.g., for subjects in hospital on Day 28; these will be compared between randomized arms using non-parametric tests (e.g., Wilcoxon's Test adapted, if necessary, to handle censoring).
- Analysis of the ordinal scale endpoints will use a proportional odds model with an indicator variable for randomized treatment. The Wald test will be used to generate a p-value comparing treatments, as well as the estimated proportional odds ratio comparing treatments with associated 95% CI.

- Analysis of AE data will primarily be descriptive based on MedDRA coding of events. The proportion of subjects experiencing an SAE and the proportion experiencing a Grade 3 or higher AE will be compared between randomized arms using Fisher's Exact Test.

For enrolled subjects who were not randomized (i.e. screen failures) or who were randomized but did not receive the treatment, the final analysis will detail safety (deaths and SAEs), and reasons they were not randomized or did not received treatment respectively.

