### 7.4 Randomization

Eligible participants will be randomized in a 1:1 ratio to either the combination group (Favipiravir and Hydroxychloroquine) or a control group. Randomization will be stratified by clinical site.

The patients will be randomized utilizing Web based data entry System. The sequence of treatment assignment will be determined prior to the start of the study.

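### The proportional odds model for the ordinal endpoints names randomised treatment only, and the Cox model leaves its terms open; adding baseline category and site to both would gain efficiency at almost no cost

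*Protocol*

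**What the plan says.** Protocol section 9.4, under the secondary endpoints, gives the ordinal model: "Analysis of the ordinal scale endpoints will use a proportional odds model with an indicator variable for randomized treatment". It goes on to name a Wald test and an odds ratio with a 95% interval. Treatment is the only term mentioned.

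For the primary endpoint, section 9.4 asks for "median time to endpoint and associated HR with 95% confidence interval; p-value from cox proportional hazard regression". Section 9.2.2 adds: "The two survival curves will be analyzed using one sided cox proportional hazard regression". Neither place names a stratum or covariate, and neither rules one out.

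On allocation, section 7.4 states: "Randomization will be stratified by clinical site". The statistical sections do not mention site again.

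The primary endpoint (section 2.3) is a two-point gain on the seven-category scale, counted from the patient's own status at randomisation, or live discharge. The flow chart in section 8 has the scale recorded at day 0.

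**The concern.** Two pieces of information are available on every patient at entry and appear in no stated model: the site, which defined the randomisation strata, and the starting category on the scale.

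The starting category matters in two ways. For the ordinal secondary endpoints it is an earlier measurement of the outcome itself. For the primary endpoint it changes what the event is. On the scale as numbered in the protocol summary, two points means:

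- from category 3 or 4, leaving hospital;
- from category 5, being in hospital without supplemental oxygen;
- from category 6, still being in hospital on supplemental oxygen.

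If a baseline factor is strongly prognostic, a model that omits it has less power than one that includes it, and its hazard ratio or odds ratio lies closer to 1. At stake is power that could be had from data already collected. The choice also bears on section 9.3, where the efficacy and futility decisions and the final test use stage-wise p-values, and the sample-size re-estimation uses the observed effect. All of these depend on which model is fitted.

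**Working it through.** **1. The plan's own figure.** Inputs from sections 9.2.1 and 9.2.2:

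- one-sided test, and "The significance level of the test is 0.025";
- "The Estimated sample size achieve 85 % power to detect a minimum of 30% reduction in the median time";
- for the effect, "This is equivalent to a Hazard ratio of 0.7", taken from medians of 11 and 7.7 days;
- for events, "50% of the patients in the control group will have clinical improvement/ discharged and 70% will have clinical improvement/discharged in the treatment arm", an average of 60% with 1:1 allocation.

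Schoenfeld's formula gives the events needed:

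d = 4 (1.960 + 1.036)² / (ln 0.7)² = 4 × 8.98 / 0.1272 ≈ 282.3, so 283 events.

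N = 283 / 0.60 = 471.7, so 472, which is the plan's figure.

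In reverse, 472 × 0.60 = 283.2 events, and power = Φ(√(283.2/4) × 0.3567 − 1.960) = Φ(1.04) = 85.1%.

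The formula contains no covariate, and the hazard ratio comes from whole-arm medians. The stated 85% therefore already describes an unadjusted comparison.

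**2. What adjustment could add to the Cox analysis.** The protocol does not give the category mix, the number of sites, or how prognostic either factor is. The following are assumptions:

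- categories 3/4/5/6 in proportions 15/60/17/8%;
- six sites, with 1:1 allocation within site;
- exponential times, censoring at day 28, about 50% control events;
- hazard ratio for improvement of 1/0.7 = 1.43 within category and site;
- N = 472, one-sided 0.025, 1,500 trials per scenario (Monte Carlo error about 1 point).

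Category effects are relative improvement hazards for categories 3/4/5/6. Site SD is on the log-hazard scale.

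| Assumed prognostic strength | HR, treatment only | HR, site-stratified and category-adjusted | Power, treatment only | Power, stratified by site only | Power, site-stratified and category-adjusted |
|---|---|---|---|---|---|
| None | 1.43 | 1.43 | 82.6% | 82.5% | 82.3% |
| Weak (1.3/1/0.7/0.5; SD 0.15) | 1.41 | 1.42 | 80.3% | 79.8% | 81.2% |
| Moderate (1.5/1/0.5/0.3; SD 0.3) | 1.38 | 1.43 | 75.2% | 76.9% | 82.1% |
| Strong (2/1/0.4/0.15; SD 0.5) | 1.35 | 1.43 | 67.8% | 71.3% | 81.9% |

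Differences from the treatment-only model:

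- category and site together: −0.3, +0.9, +6.9 and +14.1 points;
- site alone: −0.1, −0.5, +1.7 and +3.5 points.

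Most of the gain therefore comes from category. Where neither factor matters, the cost is within simulation error.

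The first row gives 82–83% rather than 85% because of the event count. With 50% control events and a hazard ratio of 1.43, treatment events are 1 − 0.5^1.43 ≈ 63%, not 70%, so about 56% of patients have events rather than 60%.

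**3. The proportional odds model.** No power figure was computed for it. The direction is the same, but the percentages above belong to the Cox model and should not be carried over.

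**The case against.** The strongest case against has four parts.

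*Deferral to the SAP.* Section 9.4 promises a fuller SAP before any between-arm comparison and presents itself as a short outline. Strata and covariates are commonly settled there. This stands for the Cox model: its silence is not an error. It does not dispose of the ordinal model, whose content is written out. The outline is also described as covering the primary endpoint, so the secondary model is stated beyond that scope.

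*Power.* A reader might infer that the primary analysis is fixed as treatment-only, so that its hazard ratio is attenuated and planned power is lost. The protocol does not support this. The Cox model's terms are open, and the treatment-only wording concerns a model that yields an odds ratio. The 85% already refers to an unadjusted contrast. A hazard ratio of 1.38 against 1.43 in the table reflects two different quantities, marginal and conditional, not a faulty estimate.

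*Prognostic strength.* Nothing in the protocol shows that baseline category is strongly prognostic. The endpoint asks for a smaller absolute recovery from category 6 than from category 3, which could offset part of the severity gradient. Categories 3 and 4 both require leaving hospital. This stands, and it is why the gain can be given only as a range that starts at zero.

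*Validity.* A reader might also infer that a chance imbalance in severity would bias the result, or that ignoring site makes the test invalid. Neither follows. Randomisation keeps the comparison valid, and the test's error rate already allows for chance imbalance. Leaving out the site strata tends to make the test conservative. Only one centre is named so far, so the number of strata is unknown.

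**Conclusion.** The point holds as a recommendation on efficiency, of minor to moderate weight. The ordinal model is stated with treatment as its only named term, although site was a randomisation stratum and the starting category is recorded at day 0. The Cox model is unspecified rather than wrong. The sample size of 472 stands, and type I error is not threatened.

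The possible gain for the Cox analysis is about 0 to 14 points of power for both factors together. It depends on the assumed category mix, six sites and the four assumed levels of prognostic strength. The protocol's figures cannot narrow that range. The case for acting is the asymmetry: almost nothing is lost if the factors are not prognostic, and something useful is gained if they are.

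**What to change.** In section 9.4, secondary endpoints, add baseline ordinal category and site (small sites pooled) to the proportional odds model beside the treatment indicator.

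In section 9.4 or the SAP, and before the interim analysis at 60% of subjects:

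- state that the primary Cox model is stratified by site (small sites pooled) and adjusted for, or stratified by, baseline category;
- give the pooling rule for small sites in advance;
- use that same model for both stage-wise p-values in section 9.3, and say which model supplies the observed effect for the sample-size re-estimation;
- keep the unadjusted Cox and proportional odds models as sensitivity analyses.

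The cost is wording only. Both variables are already available at entry, and neither the sample size nor the schedule needs to change.
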